### Participant timeline {13}

Screening for eligibility will be performed on day 50 to 10 days before prostate biopsy. Imaging by transrectal US, MRI, and PSMA-PET/CT will be performed within 1–49 days before the procedure. Histopathology of prostate biopsy specimens and risk stratification (based on imaging results and histopathology) will be performed on days 1–21. If patients are applicable and do request radical prostatectomy, the procedure will be performed risk-adapted within 22–180 days after prostate biopsy. PSA levels will be determined quarterly for 2 years, and PCA-specific diagnostic and therapeutic measures will be recorded. The timeline of the study and assessments are given in Figs. 3 and 4.

**Fig. 3 Fig3:**
[figure not shown]
DEPROMP Trial scheme

**Fig. 4 Fig4:**
[figure not shown]
SPIRIT figure of the DEPROMP Trial

### Sample size {14}

There are no published data on treatment plan changes due to the initial diagnostic performance of PET-TB to derive an optimal robust power calculation. However, the power calculation was based on pilot data suggesting inter- and intra-modal PSMA-PET/CT-dependent changes in the management plan after the detection of prostate cancer in the order of 25–75% of patients [18, 23]. Hence, we will recruit up to 230 biopsy-naïve men. The calculation of the sample size of 200 evaluable patients allows us to determine an expected rate of change in the therapeutic approach of 50% with a precision of ± 6.9% defined by the confidence interval. To allow for a dropout rate of 13%, we will recruit 230 patients. Men who drop out of the study prematurely (i.e., before the biopsies at visit 3) will be replaced by additional study participants.

### Recruitment {15}

Patients will be screened for eligibility to participate in a dedicated consultation until the target population is reached. The enrolment period will extend over 24 months.

### Assignment of interventions: allocation

#### Sequence generation {16a}

A computer-based randomization tool generates the allocation sequence and assigns participants’ biopsy results to either the SOC- or SOC and PET-TB group for review. All patients who received prostate biopsy will be randomized without further restrictions.

#### Concealment mechanism {16b}

Allocation concealment will be ensured, as the service will not release the opaque randomization code.

#### Implementation {16c}

A computerized randomization tool generates an opaque allocation sequence. Participants’ biopsy results will be assigned to either SOC or SOC and PET-TB with a 2:2 allocation.

### Assignment of interventions: blinding

#### Who will be blinded {17a}

The reporting uro-radiologists and nuclear medicine physicians are blinded to the corresponding PSMA-PET/CT or MRI results, respectively.

The reporting pathologist may know the technique used for the targeted biopsies. Otherwise, he will not have direct access to MRI or PSMA-PET/CT results.

For risk stratification and the proposal of management plans, two evaluators will be blinded by attenuating the findings of PET-TB for each patient.

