##### Prostate biopsy

The same physician performs SB and MR- and PET-targeted biopsies in one session. A pre-defined, software-assisted template is used for the institutional standardized biopsy in all participants. Due to standardization, cores 1/2/3/7/8/9 represent the outer peripheral posterolateral zone, and cores 4/5/6/10/11/12 represent the outer peripheral posteromedial zone and the central zone defined by PIRADS v2.1 sector map (Fig. 2). Biopsies will be conducted under antibiotic prophylaxis, rectal cleansing, and local anesthesia. Targeted tissue sampling will be performed from the areas classified as tumor-suspicious by MRI (PI-RADS ≥ 3) and/or PSMA-PET/CT (miPSMA ≥ 1). Up to three identified lesions on PSMA-PET/CT and/or MRI will be targeted with three biopsies per target. Software-assisted fusion technique (KOELIS Trinity®) is used for both SB and image-guided biopsies. Targeted samples are color-coded to allow for subsequent differential analysis. All biopsies are separately documented and sent for histopathological analysis.

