##### Histopathology

The analysis will be conducted according to the guidelines [4]. Specifically, specimens are labeled by location and, if applicable, whether they were obtained by SB, PET-TB, or MR-TB. Furthermore, the number of positive cores and the highest Gleason score per prostate lobe, per biopsy method, and per suspicious area (MRI and/or PSMA-PET/CT) are determined. Moreover, the loss of the tumor suppressor gene phosphatase and tensin homolog (PTEN) and PSMA expression will be determined in tumor-bearing biopsy specimens by immunohistochemistry. PSMA expression will be rated by an institutional-established valid semi-quantitative scale ranging from 0 to 3: “none,” “low,” “intermediate,” or “high,” respectively.

#### Visit 4

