### Outcomes {12}

The impact of PET/MR-TB on management intent is determined randomized by questionnaires evaluation after biopsy has been performed (Additional file 1: Appendix). Changes in management plans are any changes resulting from additional information obtained through PET-TB, including inter- and intra-modal adjustments. Diagnostic accuracy of significant cancer detection is determined using the definitions for csPCA with ISUP grade group ≥ 2. On-site radiologists will grade MRI according to PI-RADS version 2.1 [21]. PSMA-PET/CT images are evaluated per patient and per lesion according to the PROMISE miTNM classification system and the miPSMA expression score at the University Hospital Bonn [22]. PSMA expression will be rated by an established validated semi-quantitative analysis.

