However, some limitations of the study design should be noted: First, using PSMA-PET/CT in a novel instance such as PET-TB and performing it in addition to SOC results in increased costs and examination time for patients, compared to SOC methods alone. Additionally, limited access to this technology and a shortage of trained healthcare professionals must be considered when evaluating its cost-effectiveness. The benefits of incorporating PSMA-PET/CT, or modifying biopsy techniques, may also vary among patient subgroups and may not be generalizable to the entire patient population.

Although the DEPROMP Trial does not include a cost–benefit analysis or patient-reported outcomes, the data collected will provide valuable insights to assess the utility of PSMA-PET/CT as an innovative diagnostic tool for primary PCA. To fully understand the economic and societal implications of PET-TB, it is important to consider not only the monetary costs, but also the changing diagnostic landscape, as well as the patient-level perspective. In this regard, the DEPROMP study will provide results to assess the clinically relevant added value of the innovative and promising PSMA PET/CT technique.

Second, the comparison of MRI only and MRI + PSMA-PET/CT in terms of risk stratification is complicated by the fact that diagnostic workup is increased not only qualitatively but also quantitatively by a larger investigation volume. This bias could be addressed by comparing the performance of SB + MR-TB + abdominal CT and bone scan versus PET/MR-TB. However, because patients are only screened for suspected PCA, the benefit and risk to participants would not balance in this scenario. Thirdly, despite the involvement of highly qualified uropathologists, it should be noted that the histopathologic evaluation conducted within the DEPROMP study is not subject to external review. As such, it is important to take interobserver variability into account during data analysis. Finally, repeatability and transferability to other sites are questionable because examinations are performed in highly specialized tertiary referral centers.

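### The pathologist may grade targeted cores knowing whether they came from PET-TB or MR-TB; withholding the technique until the grade is signed out would cheaply remove an avoidable source of bias

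*Protocol article*

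**What the plan says.** Under blinding {17a}, the protocol article states: "The reporting pathologist may know the technique used for the targeted biopsies". The next sentence adds a safeguard: "Otherwise, he will not have direct access to MRI or PSMA-PET/CT results".

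The Histopathology section makes such knowledge likely in practice, since "specimens are labeled by location and, if applicable, whether they were obtained by SB, PET-TB, or MR-TB". The same section asks for "the number of positive cores and the highest Gleason score per prostate lobe, per biopsy method, and per suspicious area". The Prostate biopsy section adds: "Targeted samples are color-coded to allow for subsequent differential analysis".

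The grade then feeds two outcomes:

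- **csPCA detection.** Outcomes {12} states: "Diagnostic accuracy of significant cancer detection is determined using the definitions for csPCA with ISUP grade group ≥ 2".
- **Management plans.** Visit 4 bases risk stratification and plans on histopathology and imaging. Reviewers see either the full PET/MR-TB results or the SOC results with PET-TB withheld.

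The Discussion lists as a limitation that "the histopathologic evaluation conducted within the DEPROMP study is not subject to external review", and concludes that "it is important to take interobserver variability into account during data analysis".

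**The concern.** The protocol masks each group of imaging readers to the other modality, and masks two of the four plan evaluators to PET-TB. The person who sets the grade of each core is masked to imaging reports but not to the technique label. Targets come from sites that are suspicious on MRI (PI-RADS 3 or higher) or on PSMA-PET/CT (miPSMA 1 or higher). A core marked PET-TB, with its location, therefore passes on part of the index-test result while the outcome is being read.

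A borderline call between ISUP 1 and ISUP 2 leaves room for judgement. If the label sways such calls, the error need not average out as ordinary reader variability would. At stake are the first secondary outcome (added csPCA yield of PET/MR-TB over SOC), the per-method accuracy figures and, less directly, the primary proportion of men whose plan changes.

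**Working it through.** **1. The plan's own figures.** Inputs from Sample size {14}: 200 evaluable men, expected rate 50%, dropout 13%.

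- Half-width of the 95% interval: 1.96 × √(0.5 × 0.5 / 200) = 0.0693, which matches ±6.9%.
- Recruitment: 200 / (1 − 0.13) = 229.9, so 230, which matches.

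Masking the grader changes neither figure. The question is bias, not precision.

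**2. Which labels can act, and where.**

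| Core label | SOC dossier | PET/MR-TB dossier | Effect of label-dependent grading |
|---|---|---|---|
| SB | shown | shown | reaches both sides |
| MR-TB | shown | shown | reaches both sides |
| PET-TB | withheld | shown | reaches one side only |

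Bias in the comparison of dossiers thus comes mainly from PET-TB cores. Bias in the per-method csPCA results can come from any label.

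**3. Added csPCA yield.** A label-driven upgrade adds PET-TB yield only if the borderline core is a PET-TB core and neither SB nor MR-TB already shows ISUP 2 or higher in that man. Let m be the number of such men among 200, and u the difference in the probability of an ISUP 2 call caused by the label. The shift in added yield is m × u / 200. Each man moved is worth 1/200 = 0.5 percentage points. The documents give neither m nor u.

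**4. Primary proportion, illustration only.** Assume that label-aware grading produces a spurious plan change in a share b of the men with no true change. The values of b are assumptions. The true rates of 50% and 25% are the expected rate and the lower end of the range in Sample size {14}.

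- Expected observed rate: q = p + (1 − p) × b, so the shift is (1 − p) × b.
- Coverage is the probability that the 95% interval, q̂ ± 1.96 × √(q(1 − q)/200), contains p.

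| True rate p | b | Shift (points) | Coverage of p |
|---|---|---|---|
| 50% | 2% | 0.50 × 2 = +1.0 | about 94% |
| 50% | 5% | 0.50 × 5 = +2.5 | about 89% |
| 50% | 10% | 0.50 × 10 = +5.0 | about 70% |
| 25% | 2% | 0.75 × 2 = +1.5 | about 92% |
| 25% | 5% | 0.75 × 5 = +3.75 | about 78% |
| 25% | 10% | 0.75 × 10 = +7.5 | about 38% |

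The shift could be trivial or could match the planned precision. The sign is positive only because the illustration assumes that the label creates changes and never hides them.

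**5. Is this already covered?** The disclosed limitation concerns disagreement between pathologists and the lack of external review. Neither describes a grader influenced by the technique label, and no stated step addresses that.

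**The case against.** The strongest case on the other side has five parts.

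- **Masking is partial, not absent.** A reader might infer that the pathologist is unmasked. The documents do not support that: direct access to MRI and PSMA-PET/CT results is ruled out, and the wording on technique is a permission. This stands, although the labelling rule makes the permission likely to be used.
- **The label says little.** PET targets include miPSMA 1, which the protocol calls equivocal, and MRI targets start at PI-RADS 3. Either label means only that imaging was suspicious, and nothing shows that PET-TB prompts more upgrading than MR-TB. This stands as to direction and size. It does not remove the asymmetry, because only PET-TB results are withheld from one dossier.
- **Grade is one input among several.** The trial is exploratory, secondary endpoints are descriptive, and the primary outcome counts any plan change, including nerve-sparing and extent of lymph node dissection, using imaging as well as histology. This stands and limits the weight of the point.
- **Labels have a use.** A reader might infer that showing technique brings no benefit. That goes too far: histology must be reported per method and per area, and results go to the patient discussion and the tumor board. What can be said is that no reason is given for the grader to see technique before the grade is fixed.
- **Later checks exist.** A reader might infer that the bias could never be corrected. The documents do not show this: tissue storage is provided for, a masked re-read is conceivable if slides are kept, and biopsy grade is compared with whole-mount histology in operated men.

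The missing external review is already disclosed and is not the point here.

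**Conclusion.** The point holds as a cheap improvement to a choice that the protocol states outright. The grader may know the technique while setting the grade that defines csPCA, and any effect of a PET-TB label would enter only the PET/MR-TB side. The added csPCA yield is exposed directly; the primary proportion is exposed through histology as one of several inputs.

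The size is not known. A reader might be tempted to state the bias as a fraction of the PET-TB benefit. The documents do not support any such figure: they give no count of men whose only core near the ISUP 1/2 boundary is a PET-TB core, no label effect and no expected added yield. What can be said is that each man moved among 200 is worth 0.5 points. Under the assumed 2 to 10% of spurious changes, the primary estimate would move by 1.0 to 5.0 points at a true rate of 50%, or 1.5 to 7.5 points at 25%, against ±6.9. Sample size and precision are unaffected.

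**What to change.** For participants not yet biopsied:

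- Submit each core with its location and a neutral core or target number. Let the link between number and technique vary by patient, with no fixed colour per technique, because a constant colour would soon be learned.
- Hold the key outside pathology.
- Add technique after the grade is signed out. The report per method and per suspicious area, and the clinical report, are then still produced.

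The cost is a changed specimen form and one linkage step before the clinical report. No extra procedure, reader or participant is needed. One limit remains: targeted cores, taken three per target beyond the 12-core template, may still be recognisable as targeted, so the masking is mainly between PET-TB and MR-TB. That is the distinction that matters most for the comparison of dossiers.

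About half of the 230 men were enrolled at submission (Trial status), so the change can reach only those still to come. For men already graded, add grading with knowledge of technique to the stated limitations, separately from interobserver variability.

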#### Procedure for unblinding if needed {17b}

The urologist who performs prostate biopsy will be provided access to all available information to perform targeted biopsies and discuss the findings with patients if indicated. Moreover, a multidisciplinary tumor board will perform the final clinical assessment and make recommendations based on all information available. Herefore, biopsy and imaging results are unblinded.

However, unblinding is not foreseen at the notional management planning level by the reviewers at any time.

### Data collection and management

#### Plans for assessment and collection of outcomes {18a}

Individual data will be collected electronically and stored in an IT system developed for the administration of this study. Participants who consent to the study will be informed and will receive an “ID number” upon entry into the study. All data will be linked using ID codes to identify the individual. A list of IDs will be kept in a secure location accessible only to the joint principal investigators. Data collection will be both paper and electronic. A summary of the data management will be included in the informed consent form given to participants. An audit trail is used to document data entry and correction.

Training of the investigators is provided prior to the start of the study and for each amendment. The questionnaires used to collect data on treatment planning were developed by the institute itself and have not yet been validated. Standardized, reliable, and validated methods are used for the laboratory tests. All data collection forms are included in the protocol.

#### Plans to promote participant retention and complete follow-up {18b}

All study data collected up to the point of patient withdrawal will be included in the final analysis. Once data are entered into the main database, it will be locked and no further changes are allowed to the original version.

To ensure continuity of study participation and complete follow-up and data collection, regular contact is made once a quarter via email.

Follow-up assessments are ideally conducted face-to-face, but can also be done by phone or mail if needed. We have chosen a time window of 3 months, as this corresponds to the guideline-compliant time window for follow-up of prostate cancer patients in the first 2 years. In addition, this time window accounts for logistical realities and promotes response to follow-up. If a participant from either group is unavailable for the follow-up interview, contact will be repeated by mail three times per measurement point.

#### Data management {19}

Original study forms will be entered and kept on file at the participating site. Participants’ files are stored in a secure and accessible place and manner. Files are stored in numerical order. Moreover, all data will be entered electronically. An audit trail is used to document data entry and correction. Errors will be detected by programs designed to detect missing data or specific errors in the data. These errors will be summarized along with detailed descriptions for each specific problem in data query reports. Access to the study data will be restricted. A password system will be utilized to control access. All reports will be prepared such that no individual subject can be identified. Functions of the database system and programs programmed with the SAS software are used to check completeness, data quality, and plausibility. After the data have been checked, queries are generated and forwarded to the responsible study physician for review and, if necessary, correction. All data will be stored on a secure server at the University of Bonn. The digital files will be stored anonymously in password-protected directories on secure computers. Detailed information on the data management procedures is deposited in the study protocol.

#### Confidentiality {27}

Patient data will be kept confidential and will not be accessible to third parties not involved before, during, and after the trial. All study data will be collected in pseudonymous form. All study-related information will be stored securely at the study site. All participant information will be stored in locked file cabinets in areas with limited access. All laboratory specimens, reports, data collection, process, and administrative forms will be identified by a coded identification number to maintain participant confidentiality. All records that contain names or other personal identifiers, such as locator forms and informed consent forms, will be stored separately from study records identified by code number. All local databases will be secured with password-protected access systems. The study protocol will be granted full public access.

#### Plans for collection, laboratory evaluation, and storage of biological specimens for genetic or molecular analysis in this trial/future use {33}

Within the DEPROMP Trial, physicians will obtain written consent from patients willing to participate in the trial including consent provisions for the collection and use of participant data and biological specimens for current and future genetic or molecular analysis (prostate tissue, blood, urine). The storage of biological samples for genetic and molecular analysis in the DEPROMP Trial takes place in the Biobank of the Medical Faculty of the University of Bonn and the University Hospital Bonn. The University of Bonn has a modern network infrastructure and clear procedures to ensure the confidentiality of the data regarding biological samples.

## Statistical methods

### Statistical methods for primary and secondary outcomes {20a}

The data collected and derived during the course of the trial will generally be presented in individual patient listings (sorted by site) and in corresponding summary tables. The summary tables will be displayed by time of assessment, if appropriate. Continuous variables will be summarized by the following statistics: number of observations, arithmetic mean, median, standard deviation (SD) minimum, and maximum. Summaries of categorical variables will show the absolute and relative frequencies by category and time of assessment. The primary endpoint will be evaluated showing the number and percentage of subjects with changing therapy algorithms due to new information through additional PET-TB together with 95% confidence limits. Secondary endpoints will be summarized descriptively. Sensitivity, specificity, and predictive values will be calculated including 95% confidence limits. Missing data are not replaced by imputation or other measures.

### Methods for additional analyses (e.g., subgroup analyses) {20b}

Exploratory subgroup analyses will be performed to investigate the possible differential effects of PSMA PET/CT imaging compared with the current standard of care. However, these analyses are based on the same statistical procedures as those previously mentioned. However, such results should be interpreted with caution because the statistical power for the required interaction effects within relevant regression models is limited.

### Methods in analysis to handle protocol non-adherence and any statistical methods to handle missing data {20c}

Missing data are not replaced by imputation or other measures.

